#### Interventions

PANDA is a telemedicine system developed through a private-public partnership in Italy, with funding from the European Union, in collaboration with the WHO. The PANDA system was designed to meet the health care needs of women during pregnancy in resource-scarce settings by expanding and standardizing ANC according to the WHO guidelines. The PANDA system, designed for use by low-skilled health care workers such as community health care workers, supported remotely by skilled personnel, aims to standardize and improve the quality of ANC visits. In addition, the system can automatically generate and provide the data necessary to measure its performance. The original PANDA system, as designed for use by community health care workers, consists of 3 integrated components (see Figure 2).

The PANDA phone: This smartphone with an Android app allows for a standardized and quality antenatal visit by using pictograms according to the national and WHO guidelines. The health care workers enter the women’s data and obstetrical and medical-surgical history into the system. The system also includes pages for medical tests to ensure that health care workers perform these tests. At the end of the visit, the PANDA phone sends the data and test results to the medical unit.The PANDA point of care: A series of medical tests are performed to screen for anemia, syphilis, HIV, malaria, eclampsia, diabetes, and malnutrition. The test results are entered manually or via Bluetooth into the PANDA phone.PANDA medical unit: A database system receives data from the PANDA phone, establishes diagnoses and the management of pregnant women, and maps pregnancies in the region. The PANDA medical unit in the maternity ward typically consults this database.

**Figure 2 figure2:**
[figure not shown]
The Pregnancy and Newborn Diagnostic Assessment system. PANDA: Pregnancy and Newborn Diagnostic Assessment.

The PANDA system used in our proposed study is like the system used in the pilot feasibility and acceptability study in 2016 [21]. It has already been adapted to the Burkinabè context. The PANDA system will be integrated into the Burkinabè health system and used by the Ministry of Health’s care providers in the health center under the supervision of the district management team. The PANDA app and the PANDA medical unit will be readapted to the new national norms and standards for ANC, which are currently under revision based on the new “WHO Recommendations on Antenatal Care for a Positive Pregnancy Experience” [4]. To adapt the tool to other telemedicine systems in practice in Burkina Faso, tablets have replaced smartphones. A user’s manual for the PANDA app was made available to the stakeholders for the judicious use of the app. We organized several forms of training to explain better the use of the PANDA app (user training at the health center and medical unit levels).

#### Outcomes

The primary outcome is a binary variable derived from the quality score. It will be coded 1 (yes) for women with at least 75% of the total score and 0 if not (Table 1). The quality score considers all the components of good ANC according to the gestational age of the pregnancy. The different components are grouped into 7 main dimensions with items. These items are derived from Burkina’s guidelines on ANC [23]. The categorization is that each woman has a total score for each ANC (from the first consultation to the last).

**Table 1 table1:** Summary of the components of quality antenatal care.

Item (1 if yes, 0 if no)	Data source
Antenatal consultation performed	Woman’s health card reports
Partner’s presence at the consultation	Item asked to the woman
Possession of a verified health record	Woman’s health card reports
Pregnancy test performed	Woman’s health card reports
Date of last period requested	Item asked to the woman
Probable date of delivery given to the pregnant woman	Item asked to the woman
Hypertension was investigated	Item asked to the woman
Asthma was investigated	Item asked to the woman
Testing for sickle cell disease	Item asked to the woman
Diabetes was investigated	Item asked to the woman
Surgical history was obtained	Item asked to the woman
Number of pregnancies was queried	Woman’s health card reports
Number of deliveries was queried	Woman’s health card reports
Number of abortions or miscarriages was queried	Woman’s health card reports
Number of caesarean deliveries was queried	Woman’s health card reports
Number of living children was queried	Woman’s health card reports
Alcohol consumption queried	Woman’s health card reports
Tobacco use queried	Woman’s health card reports
Sugar and albumin levels in the urine measured	Woman’s health card reports
Syphilis test performed	Woman’s health card reports
An HIV test was offered to the woman	Woman’s health card reports
HIV test was performed	Woman’s health card reports
Blood pressure measurement	Woman’s health card reports
Fetal heart sounds recorded	Woman’s health card reports
Search for edema of the feet and face	Woman’s health card reports
Weight gain	Woman’s health card reports
Temperature checks	Item asked to the woman
Physical examination: uterine height measured	Woman’s health card reports
Physical examination: vaginal touch performed	Woman’s health card reports
Physical examination: decision on obstetrical prognosis (normal pelvis, borderline pelvis, etc)	Woman’s health card reports
Tetanus vaccination verified and performed	Woman’s health card reports
Hepatitis B vaccination verified and performed	Woman’s health card reports
Antianemia prophylaxis (iron–folic acid) prescribed	Woman’s health card reports
Antianemia prophylaxis: woman explains dosage correctly	Item asked to the woman
Prescribed antimalarial prophylaxis	Woman’s health card reports
Malarial prophylaxis: woman explains dosage correctly	Item asked to the woman
Danger signs of pregnancy explained to the woman	Item asked to the woman
Place of delivery discussed	Item asked to the woman
Importance of exclusive breastfeeding explained	Item asked to the woman
Early breastfeeding of the baby has been advised	Item asked to the woman
Maternal nutrition: good feeding practices discussed	Item asked to the woman
Postpartum contraception was discussed	Item asked to the woman
Use of an impregnated net was explained	Item asked to the woman
Newborn care was explained	Item asked to the woman
The childbirth preparation plan was discussed	Item asked to the woman
The woman was asked to raise concerns where appropriate	Item asked to the woman
The next meeting was negotiated	Item asked to the woman
Summary of the antenatal care written in the woman’s health record	Woman’s health card reports

The secondary outcomes to measure include the satisfaction of pregnant women (measured at each ANC), women’s knowledge on birth preparedness and complication readiness (measured in the first trimester and just before delivery), use of maternal health services, men’s involvement in health service use (defined as the proportion of men who accompany their wives to the health centers for ANC sessions and delivery and the proportion of men who attended an ANC session or delivery), and finally, the women’s use of postpartum family planning (measured at the sixth week postpartum).

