### Study Objectives and Hypothesis

The objective of this study was to evaluate the effects of the PANDA system on the quality of ANC in Burkina Faso. We hypothesize that the PANDA telemedicine system improves (1) the quality of ANC provided to pregnant women, (2) women’s satisfaction, (3) women’s knowledge on birth preparedness and complication readiness, (4) maternal and child health service use, (5) men’s involvement in maternal health service utilization, and therefore (6) postpartum contraception use.

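### The primary quality-of-care score counts the partner's attendance, which is not care provided and is also part of the secondary outcome on men's involvement

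*Protocol article*

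**What the plan says.** The first hypothesis in the protocol article (Study Objectives and Hypothesis) concerns the quality of ANC that women are provided. A separate one is "5) men’s involvement in maternal health service utilization".

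Under Outcomes, the primary outcome is derived from a quality score: "It will be coded 1 (yes) for women with at least 75% of the total score and 0 if not". Table 1 lists the items, each scored 1 or 0 with no weights given. The second row is "Partner’s presence at the consultation Item asked to the woman".

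The same section lists men's involvement among the secondary outcomes, "defined as the proportion of men who accompany their wives to the health centers for ANC sessions and delivery", together with the proportion of men who attended an ANC session or the delivery. Nothing in the article removes the partner item from the primary score.

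The section also says that the items derive from the national ANC guidelines and that the score takes account of gestational age. Statistical Methods plans unadjusted and adjusted comparisons, with adjustment for unbalanced sociodemographic factors and women's autonomy.

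**The concern.** A partner's attendance is not an act of the provider. Two women who receive identical care can therefore be coded differently on an outcome that is meant to describe that care.

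This would matter little if attendance were unrelated to allocation. But the protocol predicts that the intervention raises men's involvement, so any resulting error runs in the hypothesized direction. Adjusting for sociodemographic factors and autonomy would not remove it, because attendance is part of the outcome and is not a baseline imbalance.

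At stake is the interpretation of a positive primary result: how much of it reflects better care, and how much reflects more partners coming along. The economic evaluation values gains in ANC quality, so it could inherit the same ambiguity if it uses this score.

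**Working it through.** **The plan's own figures.** The Sample Size section plans for 80% versus 65%, a 15-point difference. Its size reproduces:
- 138 women per arm (5% two-sided, which is assumed; 80% power).
- 138 × 1.585 = 218.7, and 218.7 / 40 = 5.47, so 6 centers, or 240 women.
- 240 × 1.10 = 264.

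No input depends on which items are in the score, so the sample size is unaffected. The 15 points serve here only as a yardstick.

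**Weight of the item.** Table 1 as printed has 48 items. With equal weights and all items applicable (an assumption, since the score depends on gestational age):
- Cut: 0.75 × 48 = 36 items.
- Share of the partner item: 1/48 = 2.1%.

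**Identical care, different code.** Take a woman who meets 35 of the other 47 items:
- Partner absent: 35/48 = 72.9%, coded 0.
- Partner present: 36/48 = 75.0%, coded 1.

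**Score without the item.** 0.75 × 47 = 35.25, so 36 of 47 are needed. When all items apply, the only women recoded are those with exactly 35 other items and a partner present: 35/47 = 74.5%, so 1 becomes 0.

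Where fewer items apply, the recoding can go the other way. With 45 applicable items including the partner's, a woman with 33 others and no partner scores 33/45 = 73.3% (coded 0). Without the item she scores 33/44 = 75.0% (coded 1). A fixed integer cut would therefore be wrong; the 75% must be applied to the applicable items.

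**Possible shift in the primary proportion (illustration only).** The article gives neither the score distribution nor attendance rates. Assume a roughly normal score with SD 3 to 6 items, 65% passing in the comparison arm, and arms that differ only in attendance. If attendance differs by a fraction a, the mean score moves by d = a × 1 item, and

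shift = Φ(z₀.₆₅ + d/SD) − 0.65, with z₀.₆₅ = 0.385.

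| Attendance difference | SD 3 | SD 6 |
|---|---|---|
| 20 points (d = 0.2) | Φ(0.452) − 0.65 = 2.4 points | Φ(0.419) − 0.65 = 1.2 points |
| 10 points (d = 0.1) | Φ(0.419) − 0.65 = 1.2 points | Φ(0.402) − 0.65 = 0.6 points |

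At a 20-point attendance difference, the shift is about 8% to 16% of the planned 15 points (1.2/15 to 2.4/15).

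**The case against.** **The score is defined broadly.** It covers the components of good ANC under national guidelines, not provider acts alone, and the partner's presence may be one of them. That explains why the item is there. It does not make attendance care provided, which is how the first hypothesis is worded, and it does not remove the overlap with the other hypothesis.

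**One item in 48 is minor, and any dichotomized composite has women near the cut.** Both points are true, and they limit the size of the problem. What sets this item apart is that the trial expects the intervention to move it by a route other than care.

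**Changing the primary outcome now would be worse.** Data collection ended in September 2022 and the analysis is reported complete in June 2023, in an unblinded trial. This objection stands in full and is why the published score should remain primary.

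A reader might also infer stronger points that the article does not support:
- *That "Antianemia prophylaxis: woman explains dosage correctly" and "Malarial prophylaxis: woman explains dosage correctly" contaminate the score in the same way.* On the same assumptions, a 20-point difference in all three items would give about 3.6 to 7.1 points, but most of that comes from the dosage items. Women were questioned immediately after the visit (Data Collection Methods), and Table 1 has no other item on dosage counseling. These items therefore partly measure how well the provider explained the dose, which is an intended effect.
- *That the item recording that a consultation took place is always 1 and distorts the result.* That it is constant is an inference. A constant item would not by itself create a difference between arms.
- *That the trial claims two independent confirmations.* It does not. Men's involvement is secondary and also covers delivery.

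**Conclusion.** The point holds for the partner item. The same behavior contributes to the primary outcome on quality of ANC provided and to the secondary outcome on men's involvement. An effect on attendance would pass into the primary result without any change in care.

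The likely size is small: 2.1% of the score if all 48 items apply with equal weight, and about 1.2 to 2.4 points on the primary proportion for a 20-point attendance difference. Those points rest on assumed values for the SD, the pass rate and the attendance difference, so they indicate scale and do not estimate bias. The finding does not invalidate the primary outcome, does not touch the sample size and does not justify redefining the outcome. It limits what a positive result can be said to show, most of all if the observed effect is modest.

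**What to change.** Keep the published score and its 75% cut as the primary outcome. Beside it, report a sensitivity analysis that:
- drops the partner item from both numerator and denominator;
- applies the 75% cut to the items applicable at each visit, not a fixed integer count;
- is otherwise identical to the primary analysis.

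Attribute a primary effect to better care provided only if this version leads to the same conclusion. Report partner presence under men's involvement. A further version without the two dosage items is optional; if shown, say that it also removes the score's only measure of dosage counseling.

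The data are already collected, so the cost is a few lines of code and one table row. The drawback is timing: the analysis must be labeled as added after data collection, and it qualifies the primary result without replacing it.

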#### Other Variables

We collected women’s sociodemographic characteristics such as women’s age, education, marital status, residence, and occupation. We also collected data on women’s autonomy (Multimedia Appendix 1). We asked the women, in some situations, regarding who makes the final decision: herself, her husband, mother-in-law, father-in-law, or any other person. She could name more than one person if the decision was made collectively. These autonomous situations or items could be small household expenses, major household expenses, women’s expenses, women’s job, buying children’s clothes, where to go for advice if her child is ill, where to go to see a doctor if she is ill, buying medicines, visiting her parents (when or where), number of children in her household, and using the family planning method. The woman’s autonomy variable will be derived from these variables (composite index) and will have 3 modalities (low autonomy, moderate autonomy, and high autonomy).

#### Sample Size

In addition to the desired statistical power and percentage of potential lost to follow-up, the calculation of the required size considered several statistical features inherent to the design of the study, such as the number of participants per cluster, the intraclass correlation coefficient (ICC), and the inflation factor [24-27]:

Number of participants: To be practical and comfortable with data collection, we considered 40 women per health center, excluding those lost to follow-up.ICC: This measures the extent of the cluster effect and assesses the degree of similarity between the individuals within a cluster. It is based on the relationship between the intercluster variance and the intracluster variance. For this reason, the sample sizes must be increased to account for the clustering effect. In particular, the value of ICC depends on the unit of randomization and the type of outcome. In our case, we have women likely to come from the rural areas of several health zones. Given the composition of health care workers in rural health centers (midwives and birth attendants), it is reasonable to assume that there will be slight variations between women moving from one health center to another. For this, we propose an ICC of 0.015.Inflation factor: The increase required to account for the cluster effect is influenced by ICC and cluster size. The standard sample size was increased by an inflation factor equal to [1 + (n – 1) ρ], where n is the average cluster size and ρ is the estimated ICC. By numerical application, inflation factor = 1.585.The desired statistical power was 80%.The margin of error was 5%.The estimated proportion of those lost to follow-up was set to 10%.

Using Stata 15.1 software [28], health centers needed to detect a difference of at least 15% (80% in the intervention group vs 65% in the control group) in the proportion of women with an excellent ANC quality score in 6 health centers in each group. Considering the loss to follow-up proportion at 10%, the minimum final size required is 264 women in each group with 12 health centers, except the urban health facility. The hypothetical proportion of 65% in the comparison group was derived from a study conducted in Ghana in 2019 by Baafi et al [29].

#### Participant Recruitment

The health care providers recruited the participants during the ANC sessions after history taking and physical examination. After screening a potentially eligible woman, her consent (free and informed decision) to participate in this study was obtained after she received all the necessary information from the data collector.

#### Randomization

Facilities were randomized using a matched-pair method. Health centers were selected by identifying 6 pairs of comparable health centers. The matching criteria were (1) number of total ANC visits in the year before the trial, (2) number of total deliveries in the year before the trial, (3) number of total postnatal care visits in the year before the trial, (4) number of women of childbearing age in the health center area, (5) total number of health care workers in the health center as well as the distribution by profile (midwives, nurses, and auxiliary birth attendants), and (6) size of the population served. These matching variables allow us to obtain facilities within each pair that are similar to each other regarding these matching factors. Within each pair, the center that received the PANDA app was chosen randomly using the draw of 1 health center from each pair; the names of the health centers were previously arranged in individual envelopes and sealed. The drawer was different from the one who prepared the envelopes and did not attend the sealing. The draw, therefore, was carried out 6 times. All consecutive and eligible participants were included in the clusters.

To assess women in the semiurban environment (city of Koupéla), we included the health center in Koupéla, which unfortunately could not be matched to another city, given its size and characteristics. To minimize the likelihood of cross-group contamination, facilities are chosen to ensure they are far enough apart. Moreover, women generally did not move from one center to another due to the distance between the health centers. They usually visit the same health center for ANC during their pregnancy. We included only the women who were sure they would realize all their ANC visits in the health center where they were included in this study. Lastly, no staff move was noted during the study between the 2 arms. The health centers selected as the study sites are shown in Table 2.

**Table 2 table2:** Study sites.

	Health center
Pair 1	Baskouré and Kalwêga
Pair 2	Boangtenga and Zaogo
Pair 3	Dialgaye and Yargo
Pair 4	Baadtenga and Sampongho
Pair 5	Gounghin and Ligdi-Malguem
Pair 6	Kabéga and Zéguédéga
One semiurban center	Koupéla health center

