**Methods:**

This is a randomized controlled trial implementing the PANDA system in 2 groups of health facilities (intervention and comparison groups) randomized using a matched-pair method. We included pregnant women who were <20 weeks pregnant during their first antenatal consultation in health facilities, and we followed up with them until their sixth week postpartum. Thirteen health centers were included, and 423 and 272 women were enrolled in the intervention and comparison groups, respectively. The primary outcome is a binary variable derived from the quality score, coded 1 (yes) for women with at least 75% of the total score and 0 if not. Data were collected electronically using tablets by directly interviewing the women and by extracting data from ANC registers, delivery registers, ANC cards, and health care records. The study procedures were standardized across all sites. We will compare unadjusted and adjusted primary outcome results (ANC quality scores) between the 2 study arms. We added a qualitative evaluation of the implementation of the PANDA system to identify barriers and catalysts. We also included an economic evaluation to determine whether the PANDA strategy is more cost-effective than the usual ANC strategy.

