### Qualitative Analysis of Factors Hindering or Facilitating Implementation

We conducted a qualitative evaluation of the implementation of the PANDA system to identify the interactions (positive or negative) between the intervention and the implementation environment. The target population comprised the intervention group and the resource personnel. The intervention group included women who had recently given birth, providers of the health centers where the PANDA system was used, and resource persons. With women, we measured mainly their perceptions of the quality of care and interactions with health providers. The health care providers were interviewed to give their opinion about the PANDA system’s technical aspects, interactions with women, and perceptions of the quality of the medical procedures provided. Given their positions in this research, the resource persons were the key informants. They were the district management team, managers of the medical unit, Directorate of Health Information Systems, Directorate of Family Health, and members of 2 nongovernmental organizations, namely, Enfants du Monde, Switzerland, and the Private and Community Initiative for Health and the Response to HIV/AIDS in Burkina Faso.

Following the reasoned approach, we performed 4 focus groups with women who had recently given birth (1 focus group per center in 4 health centers), 22 in-depth individual interviews, and again with women who had recently given birth in the 7 health centers (3 interviews per center); 18 in-depth individual interviews were conducted with the health workers of the 7 health centers (2 per center, including the medical unit). However, given the size of the CSPS Urbain (the only semiurban center), the number of health workers interviewed was 4. We also conducted 4 in-depth individual interviews with the technical and financial partners. In total, 44 individual interviews and 4 focus groups were performed.

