
### Strengths and Limitations of This Study

The limitations and challenges of this complex intervention include difficulties in coordinating with study sites and challenges related to the COVID-19 pandemic in implementing the intervention, maintaining its fidelity, and keeping the trial on schedule. Although we have designed a cluster randomized controlled trial, neither the study sites nor the participants are blinded to the study conditions because of the nature of the intervention. Moreover, the participating sites are limited to 1 rural district of Burkina Faso; thus, the results may not be generalizable at the national level (no urban facilities are included in this study). However, our results could guide countrywide policies for improving maternal and newborn health, highlighting the benefits of such an electronic decision support system for similar rural African areas where maternal and newborn morbidity and mortality rates are high.

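### The semiurban Koupéla center was never randomized but is counted in the intervention arm, where it may supply over a third of the women

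*Protocol article*

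**What the plan says.** Allocation is described in the protocol article, Randomization: "Within each pair, the center that received the PANDA app was chosen randomly using the draw of 1 health center from each pair". The section continues: "The draw, therefore, was carried out 6 times". It then turns to the semiurban site: "we included the health center in Koupéla, which unfortunately could not be matched to another city, given its size and characteristics". Table 2 lists six pairs and, on its own line, the Koupéla center. The section does not say which arm Koupéla joined or how that was decided.

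Other sections bear on the same center:

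- **Abstract, Methods:** "Thirteen health centers were included, and 423 and 272 women were enrolled in the intervention and comparison groups, respectively". The same paragraph says the two groups of facilities were randomized by a matched-pair method.
- **Sample Size:** the requirement of 264 women per group is set "with 12 health centers, except the urban health facility".
- **Qualitative Analysis of Factors Hindering or Facilitating Implementation:** "The target population comprised the intervention group and the resource personnel". It covers seven health centers and adds: "However, given the size of the CSPS Urbain (the only semiurban center), the number of health workers interviewed was 4".
- **Statistical Methods:** intention-to-treat and per-protocol comparisons of the two groups at the level of the woman, adjusted for unbalanced background characteristics of the women and for their autonomy. Nothing is said about Koupéla.
- **Strengths and Limitations:** "no urban facilities are included in this study". The non-random allocation of one center is not mentioned.

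**The concern.** Six draws within six pairs allocate 12 centers. The thirteenth entered the intervention arm by some route other than the described randomization, and it is the one center the authors judged too different in size and characteristics to match. No comparison center is semiurban, so setting and treatment are completely aligned for these women. Differences in staffing, volume or equipment between Koupéla and the rural centers enter the estimate as if PANDA had caused them. Adjustment for characteristics of the women cannot separate the two.

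An analysis of all 13 centers would therefore not be a randomized, intention-to-treat comparison, although the article presents the trial as such and its conclusion claims a high level of evidence. The same effect estimate would feed the cost-effectiveness ratio.

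**Working it through.** **1. Which arm Koupéla is in.** The qualitative study targets the intervention group and covers seven centers. Six draws give six PANDA centers, so one more must have been added, and the section names the only semiurban center among those whose staff were interviewed. The stated 18 health-worker interviews fit this: 6 centers × 2 = 12, plus 2 for the medical unit, plus 4 for the semiurban center = 18. The unequal enrollment (423 versus 272) points the same way.

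**2. The article's own sample size, which leaves this center out.** Inputs from Sample Size: 80% versus 65%, power 80%, 5% error (taken as two-sided), 40 women per center, ICC 0.015, loss 10%.

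- Individually randomized size: 138 per arm (151 with continuity correction).
- Design effect: 1 + (40 − 1) × 0.015 = 1.585.
- 138 × 1.585 = 218.7, or 5.5 centers of 40. With the correction, 239.3, or 5.98 centers. Both round up to 6 centers, or 240 women.
- 240 × 1.10 = 264, as stated.

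The stated size reproduces with 12 centers and without Koupéla.

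**3. Koupéla's share of the arm.** Enrollment by center is not given. Let r be the mean enrollment of the six drawn PANDA centers. The share is w = (423 − 6r) / 423.

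| Assumption for r | Koupéla women | Share |
|---|---|---|
| 40 (planned, before loss) | 183 | 43.3% |
| 44 (planned, with 10% added) | 159 | 37.6% |
| 45.3 (= 272/6, as in the comparison arm) | 151 | 35.7% |
| 50 | 123 | 29.1% |
| 55 | 93 | 22.0% |
| 60.4 (= 423/7, all seven equal) | about 60 | 14.3% |

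The share exceeds one third whenever r is below 423 × (2/3) / 6 = 47.

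**4. Possible bias.** Suppose the outcome rate at Koupéla differs from that of the other PANDA centers by d, for reasons other than PANDA. In a comparison that weights women equally, the arm difference shifts by w × d. The documents give no value for d, so these are illustrations:

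- w = 35.7%: d = 10 points gives 3.6 points; d = 20 points gives 7.1 points.
- w = 14.3%: 1.4 and 2.9 points.
- w = 43.3%: 4.3 and 8.7 points.

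The target difference is 15 points.

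**5. What remains without Koupéla.** The comparison arm keeps 272 women. If the drawn PANDA centers also total 272, the mean cluster size is 45.3, the design effect is 1 + 44.3 × 0.015 = 1.66, and power is about 86% on the article's inputs, with everyone followed. After 10% loss, 272 × 0.9 = 244.8 per arm, slightly above the 240 at which power is about 84%. In the least favorable row of the table the intervention arm has 240 enrolled. After 10% loss that is 216 (36 per center), with design effect 1 + 35 × 0.015 = 1.525 and effective size 216 / 1.525 = 141.6, still above the 138 needed for 80%. These figures use a normal approximation, with no allowance for the small number of clusters.

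**The case against.** The best counter-argument is that the article never says the primary test pools Koupéla. The abstract states the primary aim for rural facilities, the sample size leaves the center out, and Randomization gives it a purpose of its own: assessing women in a semiurban setting. It could be an add-on outside the randomized comparison, with the analysis set defined in a document not shown. But no such set is stated. What is stated is a two-group comparison in which the groups total 13 centers and 423 versus 272 women.

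Several narrower objections stand in part:

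- The arm is deduced, not stated, and how it was decided is not described. The deduction is firm. The documents support saying that no randomization is described for this center, but do not reveal how its arm was chosen.
- Residence, education and occupation are collected, so differences in clientele may be partly adjusted for. Center-level differences are not, nor is the unadjusted result.
- The shares are scenarios, not bounds, because all consecutive eligible women were taken. One third is reached only if the other PANDA centers average fewer than 47 women. The 20-point difference has no source in the article, and the bias could run either way.
- The article mostly calls Koupéla semiurban, so the sentence on urban facilities can be read literally. Sample Size, however, calls the excluded facility urban.
- If Koupéla enrolled more than 159 women, the remaining intervention arm is below 264. Step 5 suggests this costs little power.
- The article reports data analysis as completed in June 2023, so a restriction stated now must be dated and labelled.

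**Conclusion.** The concern holds. Twelve centers were randomized; a thirteenth, unmatched and without a described draw, is in the intervention arm and in the totals that define the comparison. The planned adjustment cannot remove center-level differences that coincide fully with the arm.

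The most natural estimate of its share is 36% of the intervention arm, assuming the drawn PANDA centers enrolled like their comparison partners; plausible scenarios run from 14% to 43%. The size and direction of the bias cannot be computed from the article. At a 36% share, a 20-point center difference would move the result by about half of the 15-point target. This must be fixed before the result is reported as randomized evidence.

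**What to change.** - Define the primary intention-to-treat population as the women of the 12 randomized centers, analyzed in their six pairs. State when this was decided and that data collection had already ended.
- Report Koupéla separately and descriptively. Show a 13-center analysis only as a sensitivity analysis labelled non-randomized.
- Restate enrollment by arm for the 12 centers, with counts by center.
- In Randomization, state Koupéla's arm and how it was assigned. In the abstract, limit the claim of matched-pair randomization to the 12 centers.
- Base the effect in the cost-effectiveness analysis on the same 12 centers.
- In Strengths and Limitations, correct the statement on urban facilities and disclose the non-random allocation. Use one term, urban or semiurban, throughout.

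The cost is a re-run of the analysis and edits to the text, with no new data. The Koupéla women leave the primary comparison, but the required 264 per group was set without them, and the 272 comparison women already exceed it. Whether the intervention arm does too depends on the counts by center.
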